### Outcomes

The primary outcome is clinical composite remission at 24 months after enrollment. Composite remission is defined as either complete remission (CR) or partial remission (PR). Secondary outcomes are CR, PR, time to remission (CR, PR, and CR or PR), no response, relapse, urine protein excretion, urinary protein creatinine ratio, serum albumin, annual change of GFR (GFR slope), PLA2R, adverse events, and composite endpoint of 40% reduction of GFR, doubling of serum creatinine, end-stage renal disease (ESRD), and death. The outcome variables and definitions are presented in Table 1.

**TABLE 1 T1:** Outcome variables and definitions.

Outcome variables	Definitions
Primary outcome	
Composite remission	Either complete remission or partial remission
Secondary outcomes	
Complete remission (CR)	A reduction of proteinuria to ≤0.3g/24 h accompanied by a normal serum albumin and a normal Scr. Beck et al. (2013)
Partial remission (PR)	At least 50% reduction from peak value of proteinuria to a level between 0.3 and 3.5 g/24 h, accompanied by an improvement or normalization of serum albumin and a stable Scr. Beck et al. (2013)
Relapse	The development of proteinuria ≥3.5 g/24 h after a CR or PR
Time to complete remission	Days from enrollment to CR
Time to partial remission	Days from enrollment to PR
No response	No reduction in proteinuria of at least 25% from baseline
Serum albumin	/
Urine protein excretion	Urine protein excretion within 24 h
Urinary protein-to-creatinine ratio (UPCR)	/
Antibodies against PLA2R	/
Doubling of serum creatinine	Doubling increase of serum creatinine from baseline
40% reduction of eGFR	A reduction in eGFR of 40% from baseline. Serum creatinine based eGFR is calculated using the Chronic Kidney disease Epidemiology Collaboration (CKD-EPI) equation
End-stage renal disease (ESRD)	eGFR ≤15 ml/min/1.73m^2^ or commencement of renal replacement treatment
Composite endpoint	ESRD or 40% reduction of eGFR or doubling of serum creatinine
eGFR slope	Annual change in eGFR

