### Sample Size

The composite remission rate in Chinese adults with IMN under treatment of immunosuppressive agents in clinical practice in a single center in China was 73.7% (Jiang et al., 2021). An analysis of our retrospective unpublished data from three hospitals in China showed that composite remission rate of IMN patients received CHM alone or combination therapies in clinical practice was 67.0% (75/112). Under the assumption of 10% of loss to follow-up and two-sided alpha level of 0.05, enrolment of 2000 patients would provide 80% power to detect the 2-year composite remission rate.

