### Statistical Plan

Attempting to ensure equivalence in baseline characteristics of participants between the CHM group and the conventional therapy group, a propensity score method will be performed. Variables involving age, sex, proteinuria, eGFR, serum albumin, uric acid, PLA2R antibody level, and pathological type will be included into the logistic regression model to calculate a propensity score for each participant. Participants who are exposed to CHM will be matched to those who receive conventional drugs alone based on the propensity score, using the greedy matching with a standard calliper width of 0.2 and without case replacement. Covariate balance of the matched cohort will be assessed using the mean standardized differences. When a |d| > 0.10, it is considered as an imbalance. Inverse probability of treatment weighting based on the propensity score will also be performed to evaluate the robustness of the matching results.

Baseline demographic variables will be presented as means, medians, or percentages, and using Chi-square test, independent t test, or Mann-Whitney *U* test, as appropriate. Outcomes of composite remission, CR, PR, no response, death, relapse, and composite endpoint will be analysed by using Chi-square test and logistic regression. Odd ratios and 95% confidence intervals will be estimated. Time to remission will be analysed by using Cox regression model, adjusting for gender, age, baseline proteinuria, GFR, PLA2R antibody level, uric acid, Chinese medicine syndrome, and propensity score.

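### Relapse can occur only after remission, yet it is analysed as a plain binary outcome with no risk set and no time at risk, so the regimen comparison on relapse is hard to interpret whichever denominator is used

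*Protocol article*

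**What the plan says.** The protocol article, Outcomes (Table 1), defines relapse as "The development of proteinuria ≥3.5 g/24 h after a CR or PR". A patient who has never remitted therefore cannot relapse.

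The Statistical Plan gives the method: "Outcomes of composite remission, CR, PR, no response, death, relapse, and composite endpoint will be analysed by using Chi-square test and logistic regression", with odds ratios and 95% confidence intervals. Survival methods are named for one outcome only: "Time to remission will be analysed by using Cox regression model".

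The comparison groups are formed at baseline: "Participants who are exposed to CHM will be matched to those who receive conventional drugs alone based on the propensity score". Inverse probability of treatment weighting on the same score checks robustness. No sentence says who belongs in the relapse analysis or from when a patient is counted as at risk.

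**The concern.** Six of the seven outcomes in the list can be assessed in every matched patient. Relapse cannot, because it needs an earlier remission, and remission is itself the primary outcome and may differ by regimen. A two-by-two table of relapse by regimen then has two possible denominators, and each causes difficulty.

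- **All matched patients.** Patients who never remitted sit among those without relapse, which is the favourable category. The comparison blends durability of remission with frequency of remission, and the frequency part runs opposite to the primary outcome.
- **Remitters only.** The groups are selected on an event after baseline, so the propensity-score balance no longer protects the comparison. A yes/no outcome also ignores how long each remitter was observed after remission.

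At stake is how a secondary outcome is read. Relapse matters to the choice between regimens, and the Introduction names a high incidence of relapse as a drawback of conventional regimens.

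**Working it through.** **Inputs from the document.** Sample Size gives composite remission of 73.7% under immunosuppressive agents (one centre) and 67.0% with CHM alone or combined (75/112 = 0.6696, which reproduces). It also gives 2000 patients and 10% loss. These remission rates are used only as an illustration; they are not estimates for the matched groups.

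**Assumptions.** The article gives no relapse rate, so the relapse risk among remitters, q, is varied from 10% to 50%. For rejection probabilities, 2000 × 0.90 = 1800 evaluable patients are split 1:1 into 900 per group. There is no planned figure for relapse to reproduce; the power statement concerns remission.

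**Reading 1: all matched patients.** Relapse proportion = remission rate × q. Set q equal in both groups, so that remitters truly relapse alike.

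Worked case, q = 20%:
- Conventional: 0.737 × 0.20 = 0.1474
- CHM: 0.670 × 0.20 = 0.1340
- Risk ratio = 0.1474 / 0.1340 = 1.10
- Odds ratio = (0.1474/0.8526) / (0.1340/0.8660) = 1.12

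| q in both groups | Conventional | CHM | Odds ratio | Chi-square rejects (nominal 5%) |
|---|---|---|---|---|
| 10% | 7.4% | 6.7% | 1.11 | 8% |
| 20% | 14.7% | 13.4% | 1.12 | 13% |
| 30% | 22.1% | 20.1% | 1.13 | 18% |
| 40% | 29.5% | 26.8% | 1.14 | 24% |
| 50% | 36.9% | 33.5% | 1.16 | 32% |

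The risk ratio is 1.10 throughout, because it equals 0.737/0.670. With remitters as the denominator (900 × 0.737 ≈ 663 and 900 × 0.670 = 603), the same truth gives an odds ratio of 1.00 in every row. The rejection column assumes that all 1800 enter the matched comparison; fewer pairs would lower it.

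*Direction.* The whole-group proportions are equal when q in the CHM group is q in the conventional group × 0.737/0.670. For 30% this is 0.30 × 1.10 = 33%. If relapse per remitter in the lower-remission group exceeds that, the higher-remission group looks better.

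*Wider gaps.* If remission were 80% v 60% (assumed; not in the article) with q = 20%, the proportions would be 16% v 12%, and the odds ratio (0.16/0.84) / (0.12/0.88) = 1.40.

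**Reading 2: remitters only.** Assume the same constant relapse rate in both groups, 20% per 12 months, with remission at month 6 in one group and month 12 in the other, both followed to month 24.
- Remission at month 6, 18 months at risk: 1 − 0.80^1.5 = 28.4%
- Remission at month 12, 12 months at risk: 1 − 0.80 = 20.0%
- Odds ratio = (0.284/0.716) / (0.200/0.800) ≈ 1.59

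The rates are identical, yet the regimen that works sooner looks worse. The months are chosen only to show the mechanism.

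**The case against.** The strongest reply is that the Statistical Plan names tests, not a denominator. A reader might infer that the plan codes never-remitters as relapse-free, and that a regimen inducing more remissions is therefore bound to look worse. The document supports neither step. No sentence keeps never-remitters in the relapse analysis, and Table 1's definition itself points to remitters as the natural risk set. A condensed article may leave that detail to a fuller plan. The bias also depends on relapse per remitter being similar, as the 30% v 33% case shows.

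That much stands. The Statistical Plan does state a restricted analysis set for ESRD, 40% eGFR reduction and eGFR slope, and none for relapse. This cuts both ways: the plan uses outcome-specific sets, but says so when it does. A denominator supplied elsewhere would not repair the method, because the binary test is unsuitable among remitters too.

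Three further points have weight:
- The size rests on assumed relapse rates, and the effect at the article's own remission rates is modest.
- The article does not say whether 73.7% and 67.0% are rates at or by a given time, and some prevalent patients may have remitted before enrolment. The share at risk could be higher and the distortion smaller.
- A whole-cohort proportion does keep the matched comparison, and remission is reported alongside it. But the odds ratio for relapse would still be read on its own.

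**Conclusion.** The point holds as a weakness in the stated method for one secondary outcome. It is not a demonstrated coding error. Relapse depends on a prior remission, but it is given a binary analysis with no risk set and no time at risk, and both available denominators give a comparison that is hard to interpret.

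On the whole-group reading, which is inferred from the fact that the only groups built are the matched or weighted ones, the spurious odds ratio at the article's remission rates is 1.11 to 1.16 over an assumed 10% to 50% relapse among remitters. It runs against the regimen with more remissions if relapse per remitter is similar, and can cancel or reverse otherwise. On the remitters-only reading, the size depends on how far the times to remission differ. The primary outcome and the sample size are not affected. The change is worth making because it is cheap and relapse is clinically important.

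**What to change.** 1. Remove relapse from the chi-square and logistic regression list.
2. Describe relapse among patients who reach CR or PR as cumulative incidence by regimen from the date of first remission, with death as a competing event. State a rule for prevalent patients already in remission at enrolment. Label this analysis descriptive.
3. For the regimen comparison, use the full matched cohort and the outcome of being in CR or PR at 24 months without an intervening relapse. Never-remitters then count as failures and the matching is kept. Present it as a supportive secondary outcome, since it overlaps the primary: composite remission at 24 months already gives no credit to a patient in relapse at that visit, so the addition mainly separates out those who relapsed and remitted again.

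The cost is plan wording and a little programming, on outcomes already planned for collection. There are two downsides. The remitter analysis is not a balanced comparison. Remission and relapse dates will also be only as precise as the visit schedule allows (quarterly in the first year, then every six months).

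### The primary 24-month remission model names no covariates while the secondary Cox model does, so residual imbalance up to 0.10 SD and Chinese medicine syndrome have no stated control in the primary comparison

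*Protocol article*

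**What the plan says.** The Outcomes section states: "The primary outcome is clinical composite remission at 24 months after enrollment". Table 1 defines remission by proteinuria together with serum albumin and serum creatinine. For partial remission, for example, the proteinuria condition is "At least 50% reduction from peak value of proteinuria to a level between 0.3 and 3.5 g/24 h".

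The Statistical Plan treats confounding in three places.

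- **Propensity score.** The variables are "age, sex, proteinuria, eGFR, serum albumin, uric acid, PLA2R antibody level, and pathological type will be included into the logistic regression model". Matching is done "using the greedy matching with a standard calliper width of 0.2 and without case replacement", and inverse probability weighting serves as a robustness check.
- **Balance rule.** "When a |d| > 0.10, it is considered as an imbalance". No action is stated for a covariate above that limit.
- **Outcome models.** For the binary outcomes: "Outcomes of composite remission, CR, PR, no response, death, relapse, and composite endpoint will be analysed by using Chi-square test and logistic regression". No covariates are listed. For time to remission, a secondary outcome, Cox regression is used, "adjusting for gender, age, baseline proteinuria, GFR, PLA2R antibody level, uric acid, Chinese medicine syndrome, and propensity score".

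**The concern.** The article gives an adjustment set for one remission analysis, and it is the secondary one. For the primary outcome it names a chi-square test, which cannot adjust, and a logistic model with unspecified content.

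This matters for two reasons. First, matching on a single score balances covariates on average. A difference of up to 0.10 SD on baseline proteinuria, albumin or eGFR passes the plan's own rule, and all three bear on how remission is defined. Without an outcome model, that difference goes straight into the odds ratio. Second, Chinese medicine syndrome is in the Cox list but not in the propensity score. The Introduction says that herbal prescriptions are individualised according to syndrome differentiation, and a secondary aim is to relate syndrome to outcome. The investigators evidently regard it as a possible confounder, since they adjust for it in the Cox model. Yet neither the matching, the weighting nor any stated covariate controls it in the primary comparison.

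**Working it through.** **The plan's own figure.** The Sample Size section gives remission of 73.7% (immunosuppressive agents) and 67.0% (75/112; herbal medicine alone or combined), 2,000 patients, 10% loss, two-sided 0.05 and 80% power. It names no contrast or allocation, so taking the difference of 73.7 − 67.0 = 6.7 points as the target is an assumption. Under 1:1 allocation:

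n = [1.960·√(2 × 0.7035 × 0.2965) + 0.842·√(0.737 × 0.263 + 0.670 × 0.330)]² / 0.067² ≈ 729 per group

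That is 1,458 in total, and 1,458/0.9 = 1,620 enrolled. With 2,000 enrolled and 1,800 evaluable, power is 87.6%. The stated 80% is therefore not reproduced at 1:1. That is a separate matter; the 6.7 points serve here only as a yardstick.

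**Covariates by analysis.**

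| Variable | Propensity score | Cox model (secondary) | Logistic model (primary) |
|---|---|---|---|
| Age, sex, proteinuria, GFR, PLA2R antibody, uric acid | yes | yes | not stated |
| Serum albumin, pathological type | yes | no | not stated |
| Chinese medicine syndrome | no | yes | not stated |

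**Bias at the tolerance limit.** Let logit P(remission) = a + b·x, with x a baseline covariate in SD units. There is no treatment effect, average remission is 70%, and the group means of x differ by d = 0.10. To first order the spurious difference is p(1 − p)·b·d = 0.70 × 0.30 × b × 0.10. Averaging the logistic curve over x gives slightly less. The documents do not give b; 0.3 to 1.0 is assumed. With 900 per group the standard error of the difference is √(2 × 0.70 × 0.30/900) = 0.0216.

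| b per SD | First-order (points) | Averaged over x (points) | Share of 6.7 | Type I error |
|---|---|---|---|---|
| 0.3 | 0.63 | 0.6 | 9% | 5.9% |
| 0.5 | 1.05 | 1.0 | 15% | 7.5% |
| 0.7 | 1.47 | 1.3 | 20% | 9.5% |
| 1.0 | 2.10 | 1.8 | 26% | 13% |

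The bias is nearly proportional to d. A total shift of 0.30 SD, as a rough stand-in for three covariates at the limit leaning the same way, gives 1.9 to 5.3 points and a type I error of 14% to 69%. That is a worst case.

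**Power.** Simulation used 1,500 replicates, true rates of 73.7% and 67.0%, and one covariate balanced between groups. It contains no matching step.

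| b per SD | 745 per group: crude / adjusted | 900 per group: crude / adjusted |
|---|---|---|
| 0.3 | 81.0% / 82.0% | 87.1% / 87.7% |
| 0.5 | 80.4% / 82.3% | 88.1% / 89.1% |
| 0.7 | 81.8% / 84.9% | 87.7% / 89.7% |
| 1.0 | 80.4% / 86.5% | 88.1% / 93.0% |

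The gain is about 1 to 6 points.

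**Precision.** With 725 per group and b from 0.3 to 1.3, the standard error of the log odds ratio rises on adjustment, from 0.116 to between 0.117 and 0.132. The power gain arises because the conditional log odds ratio lies further from zero (0.33 to 0.42, against about 0.32 to 0.34 crude).

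**The case against.** The strongest reply is that the plan nowhere calls the logistic model unadjusted. Naming it beside a chi-square test suggests that it does something more, the Abstract announces propensity score methods for both matching and adjustment, and a journal article may leave the covariate list to a fuller document. This stands: a reader might infer that the primary outcome will be analysed with no baseline covariates, but the text supports only that none are stated.

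It is also fair that the primary comparison has real confounder control. Proteinuria, albumin, eGFR and five other variables are matched on and then weighted. The 0.10 rule is a flag and does not predict that any covariate will sit there, so the bias figures are limit cases with an assumed direction and strength.

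On syndrome, the Introduction says that it shapes which herbal prescription is given. It does not say that syndrome decides whether a patient receives herbal medicine at all, so confounding of the main contrast is plausible but not documented. The plan does include a subgroup analysis by syndrome, but that does not adjust the overall estimate.

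Finally, remission at 24 months and time to remission are different quantities, since a patient may remit and then relapse. The two results could differ even with identical covariates.

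What remains is that the article fixes an adjustment set for the secondary remission analysis and not for the primary one, and that one variable on that list is left out of the propensity score.

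**Conclusion.** The point holds as one of residual confounding and an unspecified primary model. At the plan's own tolerance, one prognostic covariate could move the remission difference by about 0.6 to 1.8 points, or 9% to 26% of the 6.7-point gap. This assumes log-odds of 0.3 to 1.0 per SD, about 70% remission and a covariate exactly at 0.10; the shift grows if several covariates lean the same way. Syndrome is not a matching variable, so matching does not aim to hold its difference to 0.10.

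Two stronger readings fail. The first is that the crude analysis costs substantial power: the gain from adjustment is about 1 to 6 points, and 1,800 evaluable patients split 1:1 already give 87.6%. The second is that adjustment would make the odds ratio more precise: its standard error on the log scale rises slightly. The case for change rests on removing residual imbalance and on fixing the primary model in advance, in a registry without blinding.

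**What to change.** Make the primary analysis of 24-month composite remission a logistic regression in the matched cohort, with standard errors that respect the matching. Adjust for the prespecified propensity and Cox covariates, all at baseline: proteinuria, serum albumin, eGFR, PLA2R antibody level, uric acid, age, sex, pathological type and Chinese medicine syndrome. Report a standardised risk difference with its 95% confidence interval alongside the odds ratio. Use the same covariates in the inverse-probability-weighted analysis, and keep the chi-square test as descriptive. It would also help to state what is done when a standardised difference exceeds 0.10.

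The cost is a few sentences in the Statistical Plan and some programming, with no new data, visits or patients. One small downside is that the conditional odds ratio differs from the crude one even without confounding; the standardised risk difference handles this. Because patients may be enrolled on antibody status without biopsy, pathological type needs a stated rule for those who have none.

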### Interventions

This observational study is designed to evaluate the effectiveness of CHM in a real-word hospital setting. Therefore, there are neither treatment protocols nor interference with therapeutic schedules for the included participants. But the information of therapeutic regimens will be collected to identify the exposure of CHM. Exposure of CHM includes either oral or intravenous administration proprietary CHM products and oral administration CHM formulas. Low, moderate, and high level of CHM exposure will be defined as the cumulative exposure time of CHM accounts for 25, 50, and 75% of individual follow-up time. The individual follow-up time will be from the baseline visit to the last visit or the end of the study.

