### Enrollment and Follow-Up

This study is designed to be a long-term longitudinally extensible cohort. The study aims to include 2000 Chinese IMN adults. The recruitment is estimated to take 42 months, from July 2020 until December 2023. The patients who meet the inclusion criteria will be enrolled continuously. Both incident patients and prevalent patients will be recruited by physicians in nephrology clinics and inpatient departments in 11 participating sites. Incident patients are individuals who are newly diagnosed and first initiated on treatments. Prevalent patients are individuals who have already been diagnosed as IMN and have been receiving treatments before the study. Meanwhile, the electronic medical record in 11 participating sites will be retrospectively screened to recruit the confirmed cases.

Individuals who are eligible and consent to participate will be invited to attend a baseline visit. Participants will be followed for up to at least 2 years. Participants who experience the primary endpoint (remission) will be continued to be followed up until the end of the study or death. The schedule of follow-up visits is presented in Figure 1. Follow-up visits will occur quarterly in the first year after enrollment and then semi-annually from the second year. The baseline, semi-annual, and annual follow-up visits in the first year and annual visits from the second year are required in-person visits. All other visits can be in-person or remote via telephone call or smartphone applications. In order to retain participants and minimize the number of dropouts and withdraws as well as the missing data, a reasonably flexible visit time window within a range of 4 weeks forward or backward from the scheduled visit day will be acceptable.

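### Death, relapse and the kidney composite are compared by chi-square and logistic regression with no stated time horizon, although length of observation can differ between patients by about 42 months

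*Protocol article*

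**What the plan says.** All places are in the protocol article.

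- **Method (Statistical Plan).** "Outcomes of composite remission, CR, PR, no response, death, relapse, and composite endpoint will be analysed by using Chi-square test and logistic regression". Odds ratios with 95% confidence intervals are the effect measure. A time-to-event model is named for one outcome only: "Time to remission will be analysed by using Cox regression model".
- **Horizon (Outcomes).** "The primary outcome is clinical composite remission at 24 months after enrollment". Neither the text of that section nor Table 1 gives a time point for death, relapse or the kidney composite. Table 1 defines relapse as nephrotic-range proteinuria returning after a complete or partial remission.
- **Accrual (Enrollment and Follow-Up).** "The recruitment is estimated to take 42 months, from July 2020 until December 2023".
- **Follow-up (Enrollment and Follow-Up).** "Participants will be followed for up to at least 2 years", and "Participants who experience the primary endpoint (remission) will be continued to be followed up until the end of the study or death".
- **Individual observation time (Interventions).** "The individual follow-up time will be from the baseline visit to the last visit or the end of the study". This sentence serves to define levels of CHM exposure, but it shows that the plan expects observation time to vary by patient.
- **Adjustment (Statistical Plan).** The propensity score uses age, sex, proteinuria, eGFR, serum albumin, uric acid, PLA2R antibody level and pathological type. Enrolment date and length of follow-up are not among them.

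**The concern.** A chi-square test or a logistic regression counts whether an event was seen, not how long the patient was watched. A patient seen event-free for two years and one seen event-free for five and a half years contribute the same. That is sound when everyone is assessed at one fixed time, as for remission at 24 months. For death, relapse and the composite no fixed time is stated, while entry is staggered over 42 months and observation continues past 24 months.

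Treatment is not randomised, so nothing in the design makes observation time alike in the CHM and conventional groups, and matching on the listed covariates does not do so either. If one group tends to enrol earlier, or to stay in follow-up longer, it collects more events at the same underlying rate.

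Relapse has a second problem. Only patients in remission can relapse, so exposure begins at remission. A regimen that produces earlier remission leaves its patients longer at risk and can look worse on durability for that reason alone. At stake are the outcomes on safety, kidney survival and durability, not the primary outcome.

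**Working it through.** The plan gives no event rate for these outcomes, so there is no stated figure to reproduce. The hazards below are assumptions, shown over a range.

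**1. Range of follow-up.** Inputs: 42 months of recruitment and at least 24 months of follow-up (Enrollment and Follow-Up).
- One common closing date 24 months after last entry: last entrant 24 months, first entrant 42 + 24 = 66 months.
- Closing at the end of the five-year first phase named in the Discussion: first entrant 60 months, last entrant 60 − 42 = 18 months.
- The spread is 42 months either way.

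**2. How far risk depends on observation time.** With constant annual hazard h, risk by t years is 1 − exp(−h·t).

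| Assumed h per year | Risk at 24 months | Risk at 66 months | Odds ratio, 66 v 24 months |
|---|---|---|---|
| 1% | 2.0% | 5.3% | 2.80 |
| 3% | 5.8% | 15.2% | 2.90 |
| 5% | 9.5% | 24.0% | 3.01 |
| 10% | 18.1% | 42.3% | 3.31 |

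These are extremes between single patients, not between groups.

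**3. Effect on a group comparison when the true hazard ratio is 1.** Assume uniform entry and the 24 to 66 month range. Early-half entrants are then seen for 45 to 66 months (mean 55.5) and late-half entrants for 24 to 45 (mean 34.5). Mean risk over a uniform range from a to b years is 1 − [exp(−h·a) − exp(−h·b)] / [h·(b − a)].

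Let one group have 60% early entrants and the other 40%. Mean follow-up is 0.6 × 55.5 + 0.4 × 34.5 = 47.1 months against 0.4 × 55.5 + 0.6 × 34.5 = 42.9 months. At h = 5%, early-half risk is 20.62% and late-half risk 13.36%, so:
- group A: 0.6 × 20.62 + 0.4 × 13.36 = 17.72%
- group B: 0.4 × 20.62 + 0.6 × 13.36 = 16.27%
- odds ratio: (0.1772/0.8228) / (0.1627/0.8373) = 1.108

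| Assumed h per year | Null odds ratio, 60/40 v 40/60 | Null odds ratio, all early v all late |
|---|---|---|
| 1% | 1.100 | 1.62 |
| 3% | 1.104 | 1.65 |
| 5% | 1.108 | 1.68 |
| 10% | 1.120 | 1.77 |

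**4. When follow-up is the same in both groups.** The null odds ratio is then 1. At an assumed hazard ratio of 0.7 and h = 3%, the odds ratio is 0.694 at a fixed 24 months and 0.689 over mixed 24 to 66 month follow-up. Staggered entry alone does little harm; the distortion needs an imbalance.

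**5. Relapse at a fixed 24 months.** As an illustration, take remission at the 6-month visit against the 12-month visit. Time at risk by month 24 is 24 − 6 = 18 months against 24 − 12 = 12 months. At an assumed relapse hazard of 5% per year, the risks are 1 − exp(−0.05 × 1.5) = 7.2% and 1 − exp(−0.05 × 1) = 4.9%, an odds ratio of 1.52 with identical relapse rates. This contrasts two remission times. The effect between groups would be smaller, in proportion to how far their remission times differ.

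**The case against.** **The analysis window is not stated.** Following patients to study end describes data collection; the article does not say that these events will be counted to study end. The 24-month horizon could be meant to cover every outcome in the quoted sentence, and a condensed article may leave that to the full protocol. This stands as a limit. A reader might infer that the plan counts events over 24 to 66 months, but the documents do not say so, and that range is itself derived. What can be said is that a method needing a common horizon is named and none is given. Under a 24-month reading the problem for death and the composite shrinks to dropout; for relapse it remains.

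**Unequal follow-up does not by itself bias the comparison.** This also stands (step 4). A reader might infer that the odds ratios are necessarily biased, but nothing in the article shows that the groups will differ in entry date, dropout or time to remission, and all sites enrol continuously. The point is conditional: treatment is not randomised and the plan has no safeguard if they do differ.

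**A larger figure needs a larger assumption.** Mean follow-up of 4.0 against 3.25 years at 5% per year gives risks of 18.1% and 15.0% and an odds ratio of 1.25. That is a 9-month difference in means. With a 21-month gap between early- and late-half entrants, entry dates alone would need early-entry shares differing by 9/21 = 43 percentage points, about 71% against 29%. The 60/40 case is the more cautious illustration.

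**Losses and deaths are not simply ignored.** The Statistical Plan provides for multiple imputation and a look at reasons for missing data, and the Outcomes text counts death within the composite (Table 1 does not, a separate matter). Both are fair. Imputing missing values does not, however, equalise different administrative end dates, and death before relapse remains a competing event.

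**Conclusion.** The point holds in conditional form, for secondary outcomes only. The article fixes a binary method for death, relapse and the kidney composite without stating a horizon, in a non-randomised cohort where observation can differ by up to about 42 months and the propensity score aligns neither entry date nor follow-up. If the groups differ moderately in early entry (60/40 against 40/60), the odds ratio under no effect is about 1.10 to 1.12. This rests on assumed constant hazards of 1% to 10% per year, uniform entry, a common closing date 24 months after last entry, and events counted to that date. With balanced follow-up there is no bias under the null.

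Relapse is the firmest part: unequal time at risk persists at any horizon fixed from enrolment. Composite remission at 24 months is unaffected, and logistic regression is appropriate for it. The change should be made, but it does not threaten the main result.

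**What to change.** 1. **Death and the kidney composite.** Use Cox regression from enrolment, with censoring at the last visit. Alternatively, define a binary outcome at 24 months for everyone and state how incomplete follow-up is handled.
2. **Relapse.** Analyse time from the first remission observed in the study, with delayed entry for patients already in remission at enrolment and death as a competing event. Label the comparison as conditional on remission, since it is restricted to patients selected by a post-treatment outcome.
3. **Remission at 24 months.** Keep logistic regression.

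The cost is a little more analysis work; Cox regression is already planned for time to remission. The one data need is the remission date before enrolment for some prevalent patients, and the article does not say whether that is collected.
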